### Primary outcomes

The two primary outcomes for people with aphasia will be mood as measured by the Stroke Aphasic Depression Questionnaire- 21 item (SADQ-21) [15] and quality of life as measured by the Assessment for Living with Aphasia (ALA) [16].

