### Hypotheses

#### Primary hypothesis

People with aphasia who receive the Aphasia ASK intervention will have significantly better outcomes in mood [15] and quality of life [16] at 12 months post stroke compared to those who receive the attention control intervention (SSPIP).

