### Sample size estimates

Sample size calculations were calculated for both primary outcome measures (ALA and SADQ-21). Power calculations on the ALA have been calculated from an intensive aphasia treatment study [26] and an Australian longitudinal aphasia study [27]. Power calculations on the SADQ have been calculated from the Cost analysis of the Communication and Low Mood (CALM) study [28]. The ALA required a larger sample size compared to the SADQ-21, and therefore, the larger sample size required by the ALA was determined necessary to adequately power the study. To achieve a power of 80 % with a 5 % level of significance in comparing the two arms of the study (Aphasia ASK versus attention control - SSPIP), we need 186 patients (93 per arm) with an effect size of 0.367, computed using ALA data (26, 27). The extent to which power is diminished by clustering was considered in relation to the design effect (DE) = 1 + (m -1)r10, where m = the average size of a cluster and r is the intra-class correlation coefficient. Typically, intraclass correlation coefficients are small (<0.02); thus a conservatively estimated intra-class correlation of 0.02 was used. A cluster size of 20 was chosen based on the feasibility of running the intervention, as well as the availability of patients with aphasia within clusters. Thus DE = 1+ (20-1)*0.02 = 1.38, and the total sample size required was calculated as 186 * 1.38 ≈ 258. To account for an attrition rate of 25 % to the 12-month follow-up period, 344 patients would be needed (172 per arm).

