### Statistical analyses

Baseline characteristics of participating patients of the two arms will be presented and compared for any meaningful differences at baseline. Outcomes of interest will be analyzed on an intention-to-treat basis. Multilevel modelling using mixed models, which takes into account patients being nested within clusters, will be able to examine whether changes in the outcomes, which are on interval-scale, vary over time as well as across the two (Aphasia ASK and attention control- SSPIP) programs, after adjusting for the effects of any potential confounders (if any). In addition, attrition patterns across the two arms will be examined to determine randomness of missing data, and if required, multiple imputations will be implemented. All statistical analyses will be performed using Stata statistical software. An alpha level of 0.05 will be accepted as significant. The results of the statistical models will be presented in the form of regression coefficients, their 95 % confidence intervals, and effect sizes. The residuals of the fitted models will be examined to ensure that all required assumptions are met. The statistician completing the data analyses will be blinded to group allocation until analysis is completed.

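### Two primary outcomes share one unsplit 0.05, and a sample size set on single outcomes at the full 5% fits neither an either-outcome nor a both-outcome success rule

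*Protocol article*

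**What the plan says.** Under Primary outcomes, the protocol article makes both SADQ-21 and ALA primary: "The two primary outcomes for people with aphasia will be mood" and quality of life. The Primary hypothesis covers them in one sentence: people given the experimental programme "will have significantly better outcomes in mood [15] and quality of life [16] at 12 months post stroke".

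Statistical analyses gives a single threshold, "An alpha level of 0.05 will be accepted as significant", with no split, testing order or success rule. Results are to be shown as "regression coefficients, their 95 % confidence intervals, and effect sizes".

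Sample size estimates reports a calculation for each primary outcome and adopts the larger: "To achieve a power of 80 % with a 5 % level of significance in comparing the two arms of the study", "we need 186 patients (93 per arm) with an effect size of 0.367, computed using ALA data". It says that SADQ-21 needed fewer patients but gives no figure for it. The 186 is then inflated for clustering (design effect 1.38, giving 258) and for 25% attrition (344).

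**The concern.** One hypothesis with two outcomes can be declared successful in two ways. If either outcome is enough, testing each at 0.05 gives an overall error rate above 5%. If both are needed, a sample size that gives 80% power for one outcome gives less than 80% for the pair. Taking the larger of two single-outcome sizes at full alpha allows for neither.

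At stake is how a split result is read. If only one of SADQ-21 and ALA is significant, the trial could be called positive or negative once the data are known, and the article would not settle which.

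**Working it through.** **Inputs from the protocol article.** Two primary outcomes; alpha 0.05; power 80%; effect size d = 0.367 for ALA; 93 per arm; design effect 1.38; attrition 25%; SADQ-21 needs fewer patients than ALA. **Assumptions.** The correlation r between the two test statistics, each oriented towards benefit, is not given and is taken from 0 to 0.9. SADQ-21 power is not given and is taken from 80% to 99%.

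**1. The plan's own figure.** Per-arm n = 2(z_alpha + z_0.80)² / d².
- One-sided 5%: 2(1.645 + 0.842)² / 0.367² = 92 (93 with the t distribution). This reproduces the stated 93.
- Two-sided 5%: 2(1.960 + 0.842)² / 0.367² = 117 (118 with t). This does not.
- 186 × 1.38 = 256.7, stated as 258; 258 / 0.75 = 344. Both steps are in order.

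So 93 per arm implies a one-sided test. The article does not state sidedness, and its 95% confidence intervals correspond to two-sided 5% tests.

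**2. Either outcome suffices.** At r = 0 the family-wise error is 1 − 0.95² = 9.75%. For r > 0 it is 1 − P(neither test is significant) under a bivariate normal. The chance of a false claim of benefit from two-sided tests counts only the favourable tail: 1 − 0.975² = 4.9% at r = 0.

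| r | Two-sided, any significant result | Two-sided tests, false benefit only | One-sided 0.05 tests, false benefit |
|---|---|---|---|
| 0 | 9.75% | 4.9% | 9.75% |
| 0.3 | 9.5% | 4.8% | 9.3% |
| 0.5 | 9.1% | 4.5% | 8.8% |
| 0.7 | 8.4% | 4.2% | 8.0% |
| 0.9 | 7.0% | 3.5% | 6.8% |

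**3. Both outcomes required.** Alpha is not inflated. Joint power at r = 0 is the product of the two powers; for r > 0 it comes from the bivariate normal. With ALA power at the stated 80%:

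| SADQ-21 power | r = 0 | r = 0.5 | r = 0.9 |
|---|---|---|---|
| 80% | 0.80 × 0.80 = 64% | 69% | 75% |
| 90% | 0.80 × 0.90 = 72% | 75% | 79% |
| 95% | 0.80 × 0.95 = 76% | 78% | 80% (0.799) |
| 99% | 0.80 × 0.99 = 79% | 80% (0.797) | 80% (0.800 after rounding) |

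Joint power cannot exceed the ALA power, so the range is 64% to just under 80%.

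**4. Sidedness, a separate matter.** At 93 per arm the expected z for ALA is 0.367 × √(93/2) = 2.503. Two-sided power is Φ(2.503 − 1.960) = 71% (70.6%). If the tests are two-sided, joint power cannot exceed 71% whatever the SADQ-21 power; with SADQ-21 at 80% and r = 0 it is 0.706 × 0.80 = 57% (56.5% unrounded).

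**5. ALA power with alpha split to 0.025, at 93 per arm.** Two-sided: Φ(2.503 − 2.241) = 60%. One-sided: Φ(2.503 − 1.960) = 71%.

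**The case against.** The strongest reply is that a success rule and multiplicity handling are commonly left to the analysis plan, which is not shown, so their absence from a condensed article is no fault. That stands for the missing rule alone. It does not cover the sample size, which is fixed in the article and is built on single outcomes at the full 5%. An analysis plan that added either rule would leave that power statement unmatched to it.

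Three stronger readings are tempting, and the documents do not support them.

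- *A reader might infer that joint power is well under 80%.* The 64% needs SADQ-21 power of only 80% and independent outcomes. The article says SADQ-21 needed fewer patients, so its power should exceed 80% on the same basis, and joint power could be close to 80%. A figure such as 50% to 60% needs two-sided tests together with SADQ-21 power no higher than that of ALA. Much of that shortfall comes from sidedness rather than from having two outcomes.
- *A reader might infer a 9.8% risk of a falsely positive trial.* With two-sided tests that figure includes significant harm. The hypothesis is directional, and the risk of falsely claiming benefit is at most 4.9% when the outcomes are not negatively correlated. It reaches 9.75% only with one-sided tests. One-sided tests keep the ALA power at 80%, so the 9.75% risk of false benefit and the 71% power do not apply together.
- *A reader might infer that inflation is built into the plan.* The hypothesis joins the outcomes with *and*, which leans towards requiring both, and then no inflation arises. The article does not make this explicit as a decision rule.

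It is also fair to say that the 80% is attached to a calculation on ALA data, so the article makes no explicit claim about joint power. Even so, it presents the resulting size as adequate for the study, whose primary hypothesis covers both outcomes.

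**Conclusion.** The point holds in this form: two primary outcomes, one unsplit 0.05 and a sample size that matches neither success rule.

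- Either outcome suffices: two-sided family-wise error is 9.8% at r = 0, 8.4% at r = 0.7 and 7.0% at r = 0.9. A false claim of benefit is at most 4.9% with two-sided tests, or 9.75% with one-sided tests.
- Both required, the reading that the hypothesis favours: error is controlled, and joint power is below 80%, possibly as low as 64%, taking ALA power as stated.
- If tests are two-sided, ALA power of about 71% caps joint power at 71%. This is a sidedness problem added to the first.

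The results rest on normal test statistics, non-negative correlation over the range shown, the stated effect size and design effect, and SADQ-21 power of at least 80% except where only the cap is given.

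**What to change.** State one success rule, and the sidedness of the tests, before unblinding. If an analysis plan already contains a rule, the power statement should be brought into line with it. Two options are sound.

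1. **Both outcomes required at 0.05.** This follows the wording of the hypothesis and needs no alpha split. Replace the 80% with joint power over a range of correlations and SADQ-21 powers, and give the SADQ-21 calculation behind them.
2. **Either outcome suffices, with family-wise error held at 0.05.** Use Holm, or Hochberg if positive dependence between the outcomes is accepted. Restate power: for ALA at a 0.025 first step it is about 60% two-sided or 71% one-sided at 93 per arm. It is higher under Holm once SADQ-21 is rejected, because ALA is then tested at 0.05.

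Either option takes a sentence in the analysis section and a restated power figure. Enrolment need not change; the cost is a less favourable stated power.

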### Secondary outcomes

The secondary outcome for people with aphasia will include a 10-item measure of self-reported stroke risk-related behaviors [19]. Both ideal (for example, taking medication as prescribed) and nonideal behaviors (for example, smoking cigarettes) will be measured with higher scores out of 10 indicating performance of more ideal behaviors. Secondary outcomes for family members of people with aphasia will be the impact of caregiving measured by the Bakas Caregiving Outcomes Scale Revised (BCOS) [17] and mental health as measured by the General Health Questionnaire-28 item (GHQ) [18].

### Blinding

People with aphasia, their family members, and outcome assessors will be blinded to the study design and treatment allocation (that is, will not know there are two arms to the study). The speech-language pathologist who completes the outcome assessment will be different from the treating therapists. Unblinding of the outcome assessors will not result in the discontinuation of a participant’s involvement in the study. Attempts will be made to replace the outcome assessor if unblinding occurs and re-administration of any unblinded assessments will occur.

### Data management and monitoring body

Data will be collected and managed using REDCap, an Internet-based data capture tool designed for research studies. Clinicians from each hospital site will enter participant data directly into REDCap. Once data collection has commenced, data will be monitored for completeness and accuracy by the study’s trial manager. The study’s chief investigators will monitor study progress and adverse safety events as well as audit data accuracy on an ongoing basis. No formal criteria exist for discontinuing the trial early.

### Sample size estimates

Sample size calculations were calculated for both primary outcome measures (ALA and SADQ-21). Power calculations on the ALA have been calculated from an intensive aphasia treatment study [26] and an Australian longitudinal aphasia study [27]. Power calculations on the SADQ have been calculated from the Cost analysis of the Communication and Low Mood (CALM) study [28]. The ALA required a larger sample size compared to the SADQ-21, and therefore, the larger sample size required by the ALA was determined necessary to adequately power the study. To achieve a power of 80 % with a 5 % level of significance in comparing the two arms of the study (Aphasia ASK versus attention control - SSPIP), we need 186 patients (93 per arm) with an effect size of 0.367, computed using ALA data (26, 27). The extent to which power is diminished by clustering was considered in relation to the design effect (DE) = 1 + (m -1)r10, where m = the average size of a cluster and r is the intra-class correlation coefficient. Typically, intraclass correlation coefficients are small (<0.02); thus a conservatively estimated intra-class correlation of 0.02 was used. A cluster size of 20 was chosen based on the feasibility of running the intervention, as well as the availability of patients with aphasia within clusters. Thus DE = 1+ (20-1)*0.02 = 1.38, and the total sample size required was calculated as 186 * 1.38 ≈ 258. To account for an attrition rate of 25 % to the 12-month follow-up period, 344 patients would be needed (172 per arm).

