## Methods

### Design

This is a multicenter cluster-randomized controlled trial. Clusters, which are represented by Health Service Districts, will be randomized to either the experimental intervention or an attention control intervention, with an equal number of Health Service Districts in each arm. Usual care will continue to the intervention and control arms. The usual care provided will be at the discretion of the hospital site and their treatment protocols. Usual care is typically considered as 1 to 2 sessions of aphasia therapy per week in addition to any required rehabilitation for other stroke-related impairments. Documentation of usual care aphasia therapy will occur. Eligible individuals with aphasia and their family members will be invited to participate upon referral to speech-language pathology services, commencing intervention as early as possible in rehabilitation, but no later than 6 months post stroke. Assessments will occur at baseline and at 12 months post stroke.

The Consolidated Standards of Reporting Trials (CONSORT) 2010 extension statement for cluster-randomized trials [20] has been used to guide the research plan. The Standard Protocol Items: Recommendations for Interventional Trials (SPIRIT) 2013 statement [21] has been used to develop the trial protocol. The Template for Intervention Description and Replication (TIDieR) guide [22] has been used to guide the description of the study interventions.

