### Randomization

A factor that may affect the outcome of this study is the level of psychological services provided to patients in each cluster. A National Stroke Foundation Rehabilitation Services Report (2012) indicated that lower levels of psychological care might be provided to patients with stroke in nonurban areas in Australia. Hence, clusters will be selected in a way such that they represent either urban (capital city) or nonurban (regional/rural) areas. Considering a cluster size of 20, the required sample size of *N* = 344 (see sample size estimates for details) can be achieved from 18 clusters (nine per arm, with five in urban and four in nonurban clusters). However, 20 clusters will be recruited to account for the potential of cluster attrition during the study. See Table 1 for how the 20 clusters will be stratified. Randomization will occur using a computer-generated random number scheme. Sequential numbers will be assigned to each cluster within each stratum, and only the cluster numbers will be sent to the trial statistician to ensure allocation concealment.

**Table 1 Tab1:** Stratification of clusters

	Experimental intervention	Attention control intervention
Urban clusters (*n* = 10)	five clusters	five clusters
Nonurban clusters (*n* = 10)	five clusters	five clusters

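### The base sample size of 93 per arm matches an undeclared one-sided 5% test; the two-sided inference implied by the analysis section needs 118 per arm, so 80% power is not supported as stated

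*Protocol article*

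**What the plan says.** The protocol article, under Sample size estimates, sets out the calculation for the quality-of-life outcome (ALA), the primary outcome that determines the size of the trial:

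- Target: "To achieve a power of 80 % with a 5 % level of significance in comparing the two arms of the study".
- Result: "we need 186 patients (93 per arm) with an effect size of 0.367, computed using ALA data".
- Inflation: a design effect of 1.38 (cluster size 20, intra-class correlation 0.02) takes 186 to 258, and 25% attrition takes that to 344, or 172 per arm.

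Under Randomization, the 344 "can be achieved from 18 clusters (nine per arm, with five in urban and four in nonurban clusters"), and 20 clusters will be recruited in case some are lost. Allocation is balanced, "with an equal number of Health Service Districts in each arm".

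Under Statistical analyses, "An alpha level of 0.05 will be accepted as significant", and results will be "presented in the form of regression coefficients, their 95 % confidence intervals, and effect sizes". The primary hypothesis is worded directionally: the intervention group "will have significantly better outcomes in mood" and quality of life. The article uses neither the term one-sided nor the term two-sided.

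**The concern.** A 5% significance level with no side given, paired with 95% confidence intervals, is normally read as a two-sided 5% test. A one-sided 5% test would correspond to a 90% interval or a single 95% bound. Under the two-sided reading, the printed inputs do not lead to the printed sample size. Every later figure (258, 344 and the 18-cluster requirement) is built on the 186, so the claim of 80% power on the outcome that sets the sample size depends on a sidedness that the article never declares.

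**Working it through.** **Inputs** (all from the protocol article): standardised effect d = 0.367, power 80%, significance level 5%, equal allocation, intra-class correlation 0.02, cluster size 20, attrition 25%.

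**1. Reproduce the plan's base figure.** Normal approximation: n per arm = 2(z_α + z_0.80)² / d², with z_0.80 = 0.8416 and d² = 0.1347.

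| Test | z_α | Normal approximation | Noncentral t | Total (t) |
|---|---|---|---|---|
| One-sided 5% | 1.6449 | 92 | 92.5 → 93 | 186 |
| Two-sided 5% | 1.9600 | 117 | 117.5 → 118 | 236 |

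The one-sided t-test gives the published 93 exactly. Other readings miss it: two-sided with alpha split to 0.025 gives 142 per arm, treating 0.367 as Cohen's f gives 30 per arm, and a paired test gives 61.

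**2. Follow the plan's inflation.** 93 × 1.38 = 128.3, so 129 per arm or 258 in total; 258 / 0.75 = 344; 344 / 20 = 17.2, so 18 clusters. These steps are sound given the base figure.

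**3. Power at the base size.** At 93 per arm the t-test has 80.2% power one-sided and 70.2% two-sided (normal approximation 80.4% and 70.6%).

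**4. Two-sided, unadjusted power at the stated target.** Effective n per arm = 258 / (2 × design effect). Power = Φ(d√(n/2) − 1.96). Detectable effect = 2.8016 × √(2/n).

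| Design effect | Effective n per arm | Power | Effect detectable with 80% power |
|---|---|---|---|
| 1.38 (plan; 20 per cluster) | 93.5 | 70.9% | 0.410 SD |
| 1 + 14 × 0.02 = 1.28 (15 completers per cluster) | 100.8 | 74.1% | 0.395 SD |

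The t-test versions are 70.4% and 73.7%. Referring the test to a t distribution on 16 or 18 cluster-level degrees of freedom lowers the two rows to about 65% to 66% and about 69%.

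**5. Ceiling on recruitment.** If all 20 clusters enrolled their maximum of 20, there would be 400 enrolled and 400 × 0.75 = 300 evaluable. Two-sided power would then be 77.2% (design effect 1.38) to 80.2% (1.28).

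**6. Baseline correlation that would restore 80%.** With baseline as a covariate, the required n is multiplied by 1 − r². The unadjusted two-sided requirement before rounding is 2 × 2.8016² / 0.367² = 116.5 per arm.

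- Design effect 1.38: 1 − r² = 93.5 / 116.5, so r ≈ 0.45.
- Design effect 1.28: 1 − r² = 100.8 / 116.5, so r ≈ 0.37.

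These use the normal approximation and assume that adjustment leaves the design effect unchanged.

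**The case against.** **It is an undeclared assumption, not a slip in arithmetic.** This stands. A reader might infer that 93 is a miscalculation, or that two sentences openly contradict each other. The documents support neither: 93 is a correct answer to a one-sided question, and sidedness is simply not stated. The directional primary hypothesis could be offered as a reason for a one-sided test. However, a hypothesis that names the expected direction does not declare a one-sided test, and the article uses the same style for a secondary hypothesis that favours the control arm. If one-sided testing at 5% was intended, it needed saying, and 95% intervals do not match it.

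**The planned analysis is not an unadjusted 12-month comparison.** This also stands, and it limits the claim. A reader might conclude that the trial's true power is 71% to 74%, with a 26% to 29% chance of missing the effect. The documents do not support that. Outcomes are assessed at baseline and 12 months, and the analysis section plans mixed models of change over time with adjustment for potential confounders. Power under that model depends on a baseline-outcome correlation that the article does not give, and it could be higher or lower. With baseline as a covariate, a correlation of 0.45 would itself give 93 per arm two-sided. A pure change score would need 117 per arm at a correlation of 0.5 and 140 at 0.4. Because no correlation or adjustment appears in the sample-size paragraph, this route is possible but not shown to be the source of the figure.

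**Twenty clusters give slack.** Partly. The 77% to 80% in step 5 is a ceiling. The extra clusters are there to cover cluster loss, and the stated target remains 344.

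**Conclusion.** The point holds in this form: the base size of 186 matches a one-sided 5% t-test that the article does not declare, while the analysis section implies two-sided inference, for which the same inputs require 236. For a two-sided, unadjusted comparison at 344 enrolled, power is about 70% to 71% with the plan's design effect and about 74% with 15 completers per cluster. The corresponding detectable effects are about 0.41 and 0.39 SD.

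These figures assume d = 0.367, an intra-class correlation of 0.02, 25% attrition, no gain from baseline and a large-sample reference distribution. They show what the article's own inputs deliver under the conventional reading. They do not estimate the power of the final mixed model, which cannot be derived from the document.

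**What to change.** Keep 344 and amend the Sample size estimates section in one of two ways.

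1. Declare the primary test two-sided at 0.05. Restate power as about 70% to 71% (design effect 1.38) or about 74% (design effect 1.28), with a detectable effect of about 0.39 to 0.41 SD.
2. If the calculation is to rely on baseline adjustment, declare the test two-sided, say that baseline is a covariate, and state the assumed baseline-outcome correlation with its source. About 0.45 (design effect 1.38) or 0.37 (design effect 1.28) gives 80% two-sided power at 344.

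Either is a rewording of one paragraph. The cost of the first is a less favourable stated power; the cost of the second is an assumption that has to be justified. More enrolment is not proposed: carrying 236 through the plan's own inflation gives 236 × 1.38 / 0.75 ≈ 434, above the 400 that 20 clusters of 20 can supply.
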